## Abstract

**Introduction:**

Excessive bleeding after childbirth (postpartum haemorrhage, PPH) affects 5% of births and causes 75 000 maternal deaths worldwide annually. It is the leading cause of direct maternal deaths globally and continues to be a major cause of mortality in the UK. Oxytocin is the standard first-line treatment for atonic PPH. The PPH rate is increasing, and this may be partially related to the overuse of oxytocics in labour. Laboratory studies on myometrium suggest that repeated use of oxytocics leads to the saturation of oxytocin receptors and reduced therapeutic efficacy of oxytocin. Carboprost (a prostaglandin analogue) is usually reserved for second-line management of atonic PPH. A systematic review comparing the efficacy of carboprost and conventional uterotonics for PPH prophylaxis found that carboprost was associated with less blood loss, but around 15% of women experienced side effects. The study’s aim is to compare intramuscular carboprost with intravenous oxytocin for the initial treatment of PPH. In addition, to assess the cost-effectiveness of both treatments, participants’ views on the two treatments and the consent process.

**Methods and analysis:**

COPE is a double-blind, double-dummy, randomised controlled trial that aims to recruit 2000 women (1:1 allocation, stratified by mode of birth) across 20 hospitals in the UK. Due to the emergency nature of PPH, COPE uses a research without prior consent (RWPC) model. Randomisation and treatment will occur if eligibility criteria are met once bleeding starts. Postnatal consent will be sought for disclosure of identifiable data and continued follow-up. Clinical efficacy outcomes will be collected at 24 and 48 hours or at hospital discharge, if sooner. Questionnaires will also be collected at 24 hours and 4 weeks postrandomisation. Cost-effectiveness will be based on the incremental cost per quality-adjusted life-year, calculated from the perspective of the NHS and personal social services.

**Ethics and dissemination:**

This study has been approved by the Coventry and Warwickshire Research Ethics Committee (REC) (18/WM/0227) and the Health Research Authority. Results will be disseminated via peer-reviewed publications.

**Trial registration number:**

ISRCTN16416766.

STRENGTHS AND LIMITATIONS OF THIS STUDYThe study’s double-blind, double-dummy design reduces the risk of bias, especially for the many subjective decisions made during a postpartum haemorrhage (PPH) emergency.The use of blood transfusion as the primary outcome is not only clinically important but also reduces the potential for measurement bias.Due to the clinical emergency, a research without prior consent model is used. Experiences of this alternative to informed consent will be explored in an embedded study.The selection of the treatment pack for intended use acts as the point of randomisation, and this decentralised, clinician-led randomisation facilitates efficient recruitment during the emergency.Although PPH is common, recruitment to a multicentre study of an emergency intervention is slow as recruitment is driven by middle grade doctors who have a high work intensity and frequent turnover.

## Introduction

 Excessive bleeding after childbirth (postpartum haemorrhage, PPH), usually defined as blood loss of 500 mL, occurs after around 5% of births (depending on definition) and causes the death of 75 000 women worldwide each year.^1^ It is the leading cause of direct maternal deaths globally^2^ and continues to be a major cause of mortality in the UK.^3^ Significant maternal morbidity may also result from incapacity secondary to anaemia, delayed recovery, psychological trauma, difficulties with breastfeeding and poor bonding with the newborn. Available treatments, including drugs with known side effect profiles, blood transfusion and invasive or surgical procedures, such as hysterectomy, can have a substantial negative impact on the woman’s recovery, long-term health and sense of well-being.

PPH is a clinical emergency. The bleeding in PPH is unpredictable and difficult to quantify, so most clinicians treat it early, as soon as they feel the blood loss is excessive. Due to the unpredictability of PPH and difficulties in gaining emergency consent, there are few randomised trials of PPH treatments. The evidence used in guidelines is, therefore, based largely on prophylaxis studies and small observational studies.^4^ As a result, the National Institute for Health Research Health Technology Assessment programme called for research into PPH treatments as one of its priorities. Recent advances in emergency intrapartum consent pathways, developed partly by authors in partnership with consumer groups, have facilitated recruitment.^5^,^8^

### Rationale for chosen treatments in this study

As uterine atony is the most common cause for PPH, intravenous oxytocin is universally recommended as first-line therapy. However, the recommended dosage varies. While the National Institute for Health and Care Excellence (NICE) and WHO recommend 10 international units (IUs) intravenously; the Royal College of Obstetricians and Gynaecologists guidelines and Mothers and Babies: Reducing Risk through Audits and Confidential Enquiries across the UK (MBRRACE-UK) suggest 5 IU.^4 9 10^ There are no direct comparisons of the two doses that address efficacy. Although studies suggest that 3 IU is adequate,^11 12^ we will use a higher dose in this study (5–10 IU) to prevent criticism of inadequate dosing. The risk of this is transient hypotension that occurs with rapid injection. However, this was not seen in a recent randomised controlled trial in which 517 women were given 10 IU of oxytocin as an intravenous bolus over 1 min.^13^ The need for slow intravenous injection will be emphasised in training. Women who have a caesarean section often have intravenous oxytocin prophylaxis, a spinal anaesthetic and greater blood loss due to the surgical procedure. Therefore, participants recruited following caesarean section will be given only 5 IU, which is in line with anaesthetic recommendations.

The PPH rate is increasing, and this may be partially related to the overuse of oxytocics in labour for induction and augmentation.^10^ Laboratory studies on myometrium suggest that repeated use of oxytocics leads to the saturation of oxytocin receptors and reduced efficacy of oxytocin as a therapy.^14^ Attention has, therefore, turned to prostaglandins as an alternative approach to improving the strength of uterine contractions in the event of uterine atony. Carboprost is a prostaglandin F2a analogue that is given intramuscularly. There are 13 small studies of carboprost for PPH prophylaxis; these suggest greater efficacy but also a significant rate of adverse events that may make it less tolerable for women.^15^ Carboprost is also more expensive than oxytocin. There are no studies of carboprost for PPH treatment,^16^ but NICE recommends carboprost as a treatment. NICE and others have suggested the need for a major randomised trial to ascertain both the effectiveness of carboprost and its optimal position in a PPH treatment pathway relative to other drugs such as oxytocin.^2 4^

### Risks and benefits

Oxytocin is the standard first-line treatment for atonic PPH. It has been shown to cause effective uterine contraction, is low cost and is relatively free from side effects. Oxytocin can commonly cause headaches, nausea and vomiting. The benefit of repeated doses (eg, giving 10 IU prophylaxis and then 10 IU treatment shortly after) has been questioned,^2 17^ especially given that pharmacokinetic studies suggest that the optimal dosage is just 3 IU.^11^ Furthermore, a bolus dose of intravenous oxytocin causes a rapid but transient fall in blood pressure by around 20 mm Hg^18^ and was implicated as a contributing factor in a maternal death during PPH.^19^ It is, therefore, of uncertain benefit and not without risks.

Carboprost, a prostaglandin F2α analogue, is usually reserved for second-line management of atonic PPH. A systematic review of 13 small randomised trials comparing the efficacy of carboprost and conventional uterotonics for PPH prophylaxis found that it was associated with less blood loss, but around 15% of women experienced side effects, including diarrhoea, vomiting, fever or hypertension.^15^ It can cause bronchoconstriction in susceptible individuals and is, therefore, relatively contraindicated in those with asthma.

### Aims and objectives

The aim of this research is to assess the relative effectiveness of oxytocin and carboprost for the treatment of PPH.

The primary objective is to evaluate, in women with clinically diagnosed PPH, whether intramuscular carboprost (250 µg) is more effective than intravenous oxytocin (5 IU following caesarean section or 10 IU following vaginal birth) at reducing the need for blood transfusion after birth.

In addition, the following secondary objectives will be explored:

To assess the relative cost-effectiveness of the use of carboprost and oxytocin as initial treatments for women with clinically diagnosed PPH.To explore the views of participants and their birth partners about their experiences of the two treatments and the research without prior consent (RWPC) process.

## Methods and analysis

### Study design

COPE (The Carboprost or Oxytocin Postpartum Haemorrhage Effectiveness Study) is a double-blind, double-dummy, randomised controlled trial comparing the effectiveness of carboprost and oxytocin as the first-line treatment of PPH. The study is taking place in approximately 20 National Health Service (NHS) hospital maternity units across the UK. Due to the emergency nature of PPH, COPE uses a research without prior consent (RWPC) model; the use of which is explored within a mixed-methods substudy during the first 13 months of recruitment. Originally, in addition to RWPC, an antenatal consent pathway was used for women at increased risk of PPH. However, findings from the mixed-methods substudy led to the removal of the antenatal consent pathway. Randomisation and treatment will occur if eligibility criteria are met after childbirth. For the purposes of the recipients, anonymous data will be sent to the Liverpool Clinical Trials Centre (LCTC) for processing under public interest to allow safety monitoring. Personal identifiable information will be subsequently sent to LCTC following written informed consent.

All hospitals involved in the study give permission for data collection; these include Liverpool Women’s Hospital, Birmingham Women’s Hospital, University College London Hospital, Sunderland Royal Hospital, Burnley General Hospital, Kingston Hospital, Royal Victoria Infirmary, University Hospital of North Tees, Whittington Hospital, Queen Elizabeth Hospital (Gateshead), Medway Maritime Hospital, Poole Hospital, John Radcliffe Hospital, Leeds Teaching Hospitals, City Hospital (Nottingham), Queen’s Medical Centre (Nottingham), Kings College Hospital, Princess Royal University Hospital, Glangwili Hospital, North Tyneside Hospital and Musgrove Park Hospital.

### Eligibility criteria

Eligibility criteria for the study can be seen in box 1.

Box 1Eligibility criteriaInclusion criteria≥16 years of age.Requirement for medical treatment for primary postpartum haemorrhage (PPH).Exclusion criteria:Known to have opted out of participation antenatally.Known oxytocin or carboprost hypersensitivity.Known active cardiac or pulmonary disease.Known to have previously been treated as part of COPE (The Carboprost or Oxytocin Postpartum Haemorrhage Effectiveness Study).Has already received carboprost prophylactically for PPH.Has already received uterotonic drug treatment for PPH (this does not include PPH prophylaxis).Stillbirth.

### Interventions and treatments

Participants will be randomised in a 1:1 ratio using random variable block size, stratified by mode of birth (caesarean section or vaginal birth). The randomisation lists will be generated by a statistician at the LCTC (independent to the COPE trial) and provided to the Investigational Medicinal Product (IMP) supplier, MODEPHARMA, who will arrange IMP manufacture and distribution to sites accordingly.

The IMP will be stored at 2°C–8°C. Recruiting site pharmacies are provided with a series of sequentially numbered, sealed IMP kits, which are then distributed to an appropriate secure location within randomisation areas, that is, delivery suite, for ease of access on presentation of eligible patients.

Following confirmation of eligibility, on randomisation, the research team will select the next sequentially numbered kit for the particular mode of birth.

Each kit contains two ampoules in an outer carton. Both ampoules and the outer carton will be labelled. Each ampoule is intended for a single dose for a single participant. Each kit will contain either:

An ampoule of carboprost (250 µg intramuscular injection) and an ampoule of placebo (0.9% sodium chloride aqueous solution intravenous injection).An ampoule of oxytocin (5 IU for caesarean section or 10 IU for vaginal delivery; slow intravenous injection) and an ampoule of placebo (0.9% sodium chloride aqueous solution intramuscular injection).

The patient pathway is summarised in figure 1.

**Figure 1 F1:**
[figure not shown]
Study design schematic. IU, international unit; PPH, postpartum haemorrhage.

### Blinding

This is a double-blind study and all individuals involved in the conduct and delivery of the trial, except for the randomising statistician or those unblinded to individual cases as a requirement (eg, for safety reporting), will be blinded to treatment allocations. Statisticians involved in monitoring will be unblinded following determination of participant inclusion within each analysis population.

In case emergency unblinding is required, unblinding envelopes will be provided and stored at an agreed location within the site that is readily accessible at time of need. The construction of these envelopes is resistant to accidental damage or tampering, and contents cannot be viewed without fully opening.

### Consent

As PPH is a clinical emergency, it is not appropriate to delay treatment to seek informed consent. COPE, therefore, uses a RWPC^20^ approach where women who meet the eligibility criteria will be automatically randomised. Postnatally, once the woman is stable, and ideally within 24 hours, full study information will be provided to the woman. Before approaching women for postnatal consent, the trial recruiter will first check whether the timing is appropriate with the clinical team. Permission will be sought for disclosure of identifiable data and continued follow-up. The woman will be asked to sign the ‘postnatal (emergency pathway) patient information sheet and consent form’.

It is expected that consent will be sought for all women prior to discharge/transfer to another hospital. Where consent is not sought prior to discharge/transfer, electronic or postal consent are additional options for obtaining consent.

Originally, in addition to RWPC, an antenatal consent pathway was used for women at increased risk of PPH. Women were asked to sign the ‘antenatal patient information sheet and consent form’ during the antenatal period. In the event that the eligibility criteria were met, women who consented antenatally were randomised. If a woman made a decision antenatally not to participate, then a sticker was placed on their handheld medical notes to communicate this decision to decline participation to the clinical team. However, findings from the mixed-methods substudy led to the removal of the antenatal consent pathway and continued use of the RWPC pathway only. Copies of the participant information sheet and consent form can be found in online supplemental appendix 1.

### Sample size

We aim to recruit 2000 participants (1000 each for vaginal and caesarean section). The original sample size was 3948, based on the assumptions and supporting data described below. However, the overall event rate used within the original sample size calculation was lower than that observed and was not contained within 95% CIs produced. Following the review of the data and presentation of the overall event rate to the trial steering committee (TSC), a decision was made to reduce the trial sample size as described.

#### Original sample size calculation

To detect a 2.3% reduction in a 5.8% transfusion rate (relative risk 0.60) using a Fisher’s exact test with 90% power (alpha 0.05), we would require 1880 participants per group, increasing to a total of 3948 allowing for 5% loss to follow-up.

The magnitude of treatment effect for the primary outcome is needed to change long-established clinical practice and to represent a significant advantage, given the carboprost cost and side effects.

Data from sites and published literature provide a range of transfusion rates, the variation of which may be explained by the time point of randomisation. Table 1 demonstrates the impact of varying the event rate within this range on the study power, all other parameters including the relative effect size are maintained. Therefore, even if the transfusion rate was the lowest observed, the study would still have good power. However, the most relevant and accurate data are from a recent unpublished review of Liverpool data, and we based our sample size calculations accordingly.

**Table 1 T1:** Event rate and associated power

Transfusion rate (%)	Power (%)
3.5	71
4.0	77
5.8	90
7.5	96
10	99

Relative effect size 0.60, alpha=0.05, Fisher’s exact test.

It is planned to recruit equal numbers of women following caesarean and vaginal births to ensure that study results are convincing across both subgroups. This is to ensure that the study has the potential to impact clinical practice across both modes of birth. Within each subgroup, we would be able to detect a decrease in transfusion rate from 5.8% to 3.0% with 85% power (alpha=0.05, Fisher’s exact test).

Repeat uterotonic is an important secondary outcome, and this sample size will provide 87% power, using a χ^2^ test, to detect a 4.2% reduction from a control group rate of 23.7%.

### Outcome measures

The outcomes selected for this study include the core outcome set for PPH treatment trials^21^ and others selected in collaboration with the patient participant group. These will be collected according to the schedule in online supplemental appendix 2. Clinical efficacy outcomes will be collected at 24 hours and at 48 hours or at hospital discharge, if sooner. A 24-hour questionnaire will be administered to participants who consent on site, by site staff at the time of consent. The 4-week follow-up questionnaire will be administered to participants by site staff according to the participants’ ‘preferred method of communication for follow-up’ (email, telephone or letter) (see table 3).

**Table 3 T3:** Schedule for follow-up

Procedures	Follow-up schedule			
	Screening	Baseline (T0)*	T0–48 hours or hospital discharge if sooner	T0+4 weeks†
Assessment of eligibility criteria	X	X		
Signed antenatal consent form‡	X			
Confirmation of full eligibility by an authorised medical doctor		X		
Randomisation		X		
Administration of study intervention		X		
Signed postnatal consent form§			X¶	
Baseline characteristics		X		
Clinical outcomes				
The use and timing of additional uterotonics			X	
Manual removal of placenta			X	
Hysterectomy			X	
Blood loss at birth			X	
Non-pharmacological approach			X	
Skin-to-skin care with baby			X¶	
Separation from newborn in first hour after birth			X¶	
Breastfeeding initiation (first 24 hours)			X¶	
Blood transfusion or cell salvage			X	
Volume of blood transfusion			X	
Haemoglobin**			(X)¶	
Shock			X	
Exclusive breastfeeding (at 48 hours/discharge if sooner)			X	
Adverse reactions of particular interest		X	X	
Outcome of any organ dysfunction			X	(X)
Maternal death††		(X)	(X)	(X)
Exclusive breastfeeding (at 4 weeks)				X
Assessment of serious adverse events‡‡		X	X	(X)
Childbirth Experience Questionnaire				X
EuroQol Quality of Life questionnaire (EQ-5D-5L) including visual analogue scale (EQ-VAS)			X¶	X
Healthcare Resource Utilisation Questionnaire				X

(X)—as indicated/appropriate.

* At baseline, all procedures should be completed before study intervention.

† The participants will be contacted for follow-up using their preferred mode of communication (email, telephone or letter). If they do not respond within 2 weeks, they will receive a telephone reminder.

‡ Only for women at increased risk of haemorrhage.

§ Postnatal (emergency pathway) consent is obtained after childbirth ideally within 24 hours or prior to discharge/transfer to another hospital. If consent is not obtained prior to discharge, the appropriate consent procedures should be followed.

¶ To be completed at 24 hours after randomisation.

** Haemoglobin (in non-transfused women only) will be ideally obtained postnatally on the day following birth (12–36 hours postbirth) or at discharge, whichever is soonest.

†† All deaths collected from the time of randomisation until hospital discharge or 4 weeks, whichever is earlier.

‡‡ Serious adverse events and serious adverse reactions will be actively monitored and reported from the time of randomisation until hospital discharge or 4 weeks, whichever comes first. Adverse reactions of particular interest will be collected on a separate single timepoint eCRF.

eCRF, electronic case report form.

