#### Health economics assessments

Resource use will be based on:

Entries made in designated sections of participants’ electronic case report forms (eCRFs). The eCRFs will be used to record data on procedures (surgical) and interventions (including units of blood products transfused) and dates of patient admission and discharge. This will be collected before discharge.A resource use questionnaire (electronic, telephone or paper) will be administered at the 4-week follow-up, with a telephone reminder if no response is received within 2 weeks. The participant’s choice of how they would prefer to complete the questionnaire will be recorded on the consent form.Hospital Episode Statistics data sourced from NHS England Digital (for participants recruited in England). Data will be requested pertaining to outpatient, inpatient, critical care and emergency department attendances from 3 months prior to randomisation to 4 weeks postrandomisation (following completion of follow-up).

Unit costs will be obtained from NHS reference costs and other standard NHS sources.

Quality-adjusted life-years (QALYs) will be estimated from utilities derived from trial participant responses to EuroQol quality of life questionnaires (EQ-5D-5L) (and applying recommended methods for generating UK-relevant utilities) administered for completion at 24 hours and at 4 weeks postrandomisation. The participants will choose how they would prefer to complete the questionnaire on the consent form.

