### Data Management & Trial Monitoring

Data management and trial monitoring are delegated to the LCTC. Participants will be recruited and followed up for a maximum of 4 weeks postnatally. The recruiting hospital sites will directly enter data into a secure database. Separate data management and monitoring plans, and standard operating procedures will detail the processes conducted at the LCTC in accordance with ethical and regulatory requirements, to ensure reliability and validity of the trial data.

An independent data and safety monitoring committee (IDSMC) and TSC will oversee trial progress, and the members’ signed charters are held in the Trial Master File. Formal interim analyses of the accumulating data will be performed by LCTC at regular intervals (at least annually) for review by the IDSMC. The IDSMC will be asked to give advice to the TSC and trial management group (TMG) on whether the accumulated data from the trial, together with results from other relevant trials, justifies continuing recruitment of further patients or further follow-up. A decision to discontinue recruitment, in all participants or in selected subgroups, will be made only if the result is likely to convince a broad range of clinicians including participants in the trial and the general clinical community.

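### Deaths and serious adverse events stop being collected at hospital discharge, so new events after discharge but within 4 weeks fall outside the stated rule

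*Protocol article*

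**What the plan says.** All of this is in the protocol article.

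- Outcome measures, Table 3. The row "Maternal death" is listed among the clinical outcomes and carries an as-indicated mark at baseline, in the 48-hour/discharge column and at 4 weeks. The row "Assessment of serious adverse events" is marked as required in the first two of these columns and as indicated at 4 weeks.
- Footnote to the death row: "All deaths collected from the time of randomisation until hospital discharge or 4 weeks, whichever is earlier".
- Footnote to the serious adverse event row: serious events and reactions are "actively monitored and reported from the time of randomisation until hospital discharge or 4 weeks, whichever comes first". It adds: "Adverse reactions of particular interest will be collected on a separate single timepoint eCRF".
- Table 3 also has a row for the outcome of any organ dysfunction, marked as indicated at 4 weeks, with no discharge limit attached.
- Data Management & Trial Monitoring: "Participants will be recruited and followed up for a maximum of 4 weeks postnatally". Table 3 schedules the childbirth experience, EQ-5D-5L, breastfeeding and resource-use items at 4 weeks, with a telephone reminder for women who have not replied.
- Health economics assessments: hospital records are requested for participants recruited in England, covering the time "from 3 months prior to randomisation to 4 weeks postrandomisation".

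**The concern.** Two features of the rule matter.

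First, it leaves out events that the trial is otherwise placed to see. A woman who goes home and is readmitted within 4 weeks, or dies at home, is not within the stated collection rule. Yet the trial plans to contact consenting women at 4 weeks and, in England, to obtain their inpatient, critical care and emergency records to the same point. A readmission could be costed in the economic analysis and be absent from the safety tables.

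Second, the window has no common length. It closes at discharge, which comes after randomisation. The trial hypothesises that carboprost reduces transfusion, and the article reports side effects in around 15% of women given it for prophylaxis. Either could plausibly alter the time of discharge. Counts of deaths and serious adverse events by arm would then be taken over unequal observation times, and the article describes nothing that allows for this.

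At stake is what the trial can say about harm after a woman leaves hospital, and whether the quality-adjusted life-year (QALY) analysis can tell a woman who died after discharge from one who did not return the questionnaire. The article allows missing health outcomes to be imputed where appropriate.

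**Working it through.** The article states no figure on this point, so there is none to reproduce. The check compares the stated windows and then illustrates coverage.

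**Step 1: the windows side by side**

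| Item | Where stated | Window |
|---|---|---|
| Maternal death | Table 3 footnote | Randomisation to the earlier of discharge and 4 weeks |
| Serious adverse events and reactions | Table 3 footnote | The same |
| Adverse reactions of particular interest | Table 3 footnote | One form, single timepoint |
| Outcome of organ dysfunction | Table 3 row | To 4 weeks, as indicated |
| Questionnaires | Table 3 | 4 weeks |
| Hospital records (England) | Health economics assessments | To 4 weeks after randomisation |

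Under the two footnotes, the 4-week cells for death and serious adverse events can be filled only for a woman who has not been discharged by then. The article nowhere says that the questionnaires or hospital records feed the death or serious adverse event counts.

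**Step 2: illustrative coverage**

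Inputs: a 28-day period (4 weeks) and discharge on day d after randomisation. Length of stay is not given. The article foresees some discharges before 48 hours, but d is an assumption.

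Uncovered share = (28 − d) / 28

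- d = 1: 27/28 = 96.4%
- d = 2: 26/28 = 92.9%
- d = 3: 25/28 = 89.3%
- d = 4: 24/28 = 85.7%
- d = 7: 21/28 = 75.0%

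So discharge on day 1 to 4 leaves 86% to 96% of the days uncovered. These are shares of days, not of events. If risk is concentrated soon after birth, the share of events missed is smaller.

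**Step 3: after the change**

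With a fixed window of 28 days the planned coverage is 28/28 = 100% for each woman followed, in both arms, whatever her date of discharge.

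**The case against.** The strongest case on the other side has several parts.

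- *The table and footnotes do not strictly conflict.* The 4-week cells are marked as indicated, which fits a woman still in hospital. This stands: the issue is the window chosen, not a contradiction. The serious adverse event footnote limits active monitoring and does not say that events learned of later are discarded. The death footnote is stricter, since it governs all deaths collected.
- *Serious morbidity is largely collected elsewhere.* Hysterectomy, shock, transfusion and additional uterotonics are scheduled outcomes to 48 hours or discharge, and organ dysfunction is followed to 4 weeks as indicated. This stands and narrows the gap to new events after discharge.
- *A short window may be deliberate for a single-dose treatment, and the full protocol may say more.* Possible, but the article gives no such reason.
- *Consent comes after randomisation.* Women who decline continued follow-up cannot simply be followed to 4 weeks. This stands and limits any remedy.

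A reader might also infer two stronger things. One is that nearly all women leave safety monitoring within days. That needs a length of stay, which the article does not give. The other is that the arm with the shorter stay would look safer by a definite amount: for example, mean stays of 2.0 and 2.5 days with an equal daily event rate give 2.0/2.5 = 0.80, or 20% fewer events. Neither the half-day difference nor the constant rate has support in the document. The trial is double-blind, so stay would differ between arms only through a real drug effect, of unknown size and direction. Different stays by mode of birth would not bias the arm comparison, because randomisation is stratified by mode.

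**Conclusion.** The concern holds in limited form. As written, new deaths and readmissions after discharge but within 4 weeks are outside the stated collection rule for death and outside active monitoring for serious adverse events. Observation time is set by a post-randomisation event. The number of women affected and any bias between arms cannot be sized from the article. The 86% to 96% figure rests wholly on an assumed discharge on day 1 to 4.

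The primary outcome is untouched, and adverse and serious adverse reactions are to be reported descriptively, so no test is distorted. What changes is the reach of the safety comparison, which cannot speak to 4 weeks as it stands, and the handling of deaths in the QALY analysis. Because follow-up to 4 weeks is already planned, this is a worthwhile improvement at low cost.

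**What to change.** Amend the two footnotes so that, for women who consent to continued follow-up, maternal death, readmission and other serious adverse events are ascertained to a fixed 4 weeks after randomisation regardless of discharge.

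- **Sources.** A status check by the site at the scheduled 4-week contact, the resource-use questionnaire and, for England, the hospital data already requested. The site check is essential: a questionnaire cannot report its respondent's own death, attendance records may not show a death at home, and the linked data are requested only after follow-up and may come too late for the independent data and safety monitoring committee.
- **Reporting.** Present these events by arm over the common window. Keep the to-discharge count for non-consenting women and for active in-trial reporting.
- **Economics.** Use known death status in the QALY analysis in place of imputation.
- **Women already recruited.** The article reports at least 1062 at the sample size revision. State how they are covered, for example by linked data or a retrospective record check, so that early and late recruits do not have different windows.

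Cost: protocol wording, one status item on the case report form, a brief record check by existing staff, and more unrelated readmissions to record. Coverage will remain incomplete for women who do not consent and for participants outside England, and the report should say so.
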